## Study aims and hypothesis

The primary aim of the study is to determine the impact on gait-related gross motor skills of a gait training program using a robotic-assisted gait trainer (the Lokomat^®^Pro) compared with a gait-related physiotherapy (PT) program for children in GMFCS Levels II and III. The primary hypothesis is that children receiving the Lokomat intervention will improve more on the GMFM-66 and 6-minute walk test (6MWT) than those in the gait-related PT program.

The secondary objective is to evaluate the comparative impact of Lokomat training and gait-related PT on: (a) individualized walking/gross motor based goals; (b) the amount/location of walking the child does each day (environmental context and season considered); (c) participation in activities and (d) health-related quality of life.

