## Sample size

The study has been designed and powered to ensure adequate sample size for the primary research questions and analysis of children in GMFCS Levels II and III. The starting point for our sample size calculation consideration was a single group Lokomat study with a similar GMFCS sample and Lokomat use protocol in which the GMFM Stand and Walk mean scores changed by approximately 5 points (SD change = 7) (Borggraefe et al. 2010b). Our study is powered to let us detect a difference between the two interventions of three points (SD = 6: small effect size) on the GMFM-66, a magnitude of change that is considered to be a minimally clinically important difference (Oeffinger et al. 2008) when evaluating benefits of treatment. The reason for a difference change target in our study is that we are comparing two active interventions, each of which could result in positive change given the walking focus and boost for many of the children in therapy intensity. This sample size is also sufficient to handle the 6MWT comparisons and the small effect size observed by others in single group Lokomat studies in the 6MWT results (mean gains of 25 m [SD = 50 m], personal communication, Glenrose Hospital program, 2012).

For crossover designs, sample size calculations that link with a matched pairs *t* test calculation are appropriate (Senn 2002). A paired *t* test is also the underlying basis for the more sensitive repeated measures ANOVA that we have chosen to use so that we can include a period effect within the analysis. With an alpha of 0.025, beta of 0.20, and a detectable change score difference between intervention of thre points on the GMFM-66 (with an estimated SD of change of 6.0 points), a sample of 32 children is required (Hintze 2001). We increased the sample requirement to 40 to account for a potential drop out/protocol deviation rate of 20%. Sample calculation based on this generous drop-out rate will support the primary efficacy analysis that focuses only on the children who attend more than 70% of the sessions within one or the other intervention phase.

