## Analyses

Data entry forms were built for each measure in the study to correspond to the paper forms that the assessors used. REDCap (Harris 2012) requires outer limits for each value, and each paper data sheet is double entered for purposes of data verification process. Collectively these features optimize the data entry accuracy. Study data will be kept for seven years following conclusion of the trial, at which point data will be destroyed following REB requirements.

Descriptive statistics and graphic displays will be presented for all outcomes for the PT and Lokomat interventions (pre, post-test and change scores). Equivalence between baseline_A_ and baseline_B_ scores will be evaluated for each outcome; a t-test or Wilcoxon test will be used in this comparison as appropriate. The primary analysis will be for the pre- to post-test differences (change scores) of the GMFM-66 and 6MWT between groups. Assuming normality of data, a repeated measures ANCOVA will be performed on GMFM-66 and 6MWT change scores to compare the effects of the Lokomat and gait-related PT interventions. The child’s relevant baseline score (baseline_A_/baseline_B_) will be used in the ANCOVA to increase analytic precision. The P value will be adjusted to 0.025 to handle the expected high correlation between the GMFM-66 and timed walk. Evaluation of an intervention order effect (i.e., being the first or second treatment), as well as the interactions with intervention group will be built into this analysis (Senn 2002). Secondary sub-analyses will be done in the same way within GMFCS II and III subgroups to determine any differential response for GMFCS Level.

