A similar set of analytic approaches will be used for the secondary outcome measures (GMFM Stand and Walk, Timed Up and Go, walk velocity/step and stride length [from GAITRite], observational gait scale, average daily step counts [step activity monitor data], Quality FM, *Challenge* Assessment, ASK-30, PEDI Part II, KIDSCREEN, COPM and GAS scores), using the baseline value of the measure of interest as a covariate within a MANCOVA procedure that will permit simultaneously handling of multiple secondary outcome measure change score evaluations. If both parent and child filled out the questionnaires (i.e., all children 8 years of age and up who were able to do so), the children’s data will be analysed as primary. Otherwise parent questionnaire data will be considered as primary. A comparison of child and parent questionnaire results will be done as a secondary analysis via an ANOVA in which both single point in time (baseline) and change scores will be evaluated. ROM and Tardieu scores will be summarized in a simpler manner, using descriptive statistics and graphical presentations to illustrate scores in each phase. The power of all primary and secondary ‘no difference’ analyses will be determined post hoc.

The primary analysis will include all children who attended ≥70% of sessions for each intervention, and those who discontinued one or both interventions for a reason directly related to the study (e.g., excessive fatigue associated with participation or issues related to dislike of one or both interventions), or dropped out of the trial due to an intervention-associated injury. In the case of dropout due to study fatigue or dislike of the intervention, a strong effort will be made to do a discharge assessment at the time of withdrawal. In the case of injury, it may be possible to follow the child and evaluate some of the outcomes when the child is able (post-minor injury). If the physical assessment is not possible due to compromised physical status, completion of the functional and participation measures may still be appropriate.

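### Post hoc power is planned for null results, but on either way of computing it, it cannot say whether a 3-point GMFM-66 benefit has been excluded

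*Protocol article*

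**What the plan says.** All places are in the protocol article.

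- **Null results (Analyses).** "The power of all primary and secondary ‘no difference’ analyses will be determined post hoc". The sentence does not say whether the effect put into the power calculation is the observed one or the design target. It also does not say what will be concluded from the figure.
- **Hypothesis (Study aims and hypothesis).** The trial tests superiority: "children receiving the Lokomat intervention will improve more on the GMFM-66 and 6-minute walk test (6MWT) than those in the gait-related PT program". No equivalence or non-inferiority hypothesis is stated.
- **Target (Sample size).** The study is powered to "detect a difference between the two interventions of three points (SD = 6: small effect size) on the GMFM-66", which is called "a magnitude of change that is considered to be a minimally clinically important difference". This 3-point value is used for the sample size and is not linked to the reading of the result.
- **Error rates.** Sample size: "With an alpha of 0.025, beta of 0.20". Analyses: "The P value will be adjusted to 0.025 to handle the expected high correlation between the GMFM-66 and timed walk". Neither place says whether the test is one-sided or two-sided.
- **Baselines (Analyses).** "Equivalence between baseline_A_ and baseline_B_ scores will be evaluated for each outcome; a t-test or Wilcoxon test will be used in this comparison". No margin is given. The Design section says the six-week break is not a true wash-out, and the Analyses section adds that a return to baseline is not expected.

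**The concern.** Both arms are active gait-focused programmes, and the Sample size section accepts that each may produce improvement. A non-significant difference is therefore a realistic outcome. The question will then be whether the trial has ruled out a benefit of the size it was built to find, or has left the matter open.

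Power worked out after the data are in does not answer that. At the observed effect it contains nothing beyond the p value. At the design target it describes the trial's precision but not where the estimate fell. In either form, a reader could take a low value as a reason to dismiss the result, or a high value as proof of no difference, without justification. The sentence covers every primary and secondary outcome.

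The baseline check shares the weakness on a smaller scale. A test for a difference, with no margin, can support the word equivalence only by failing to reach significance. That depends on sample size and variability as much as on the true shift.

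**Working it through.** **Inputs.** From Sample size: difference 3 points, SD 6, alpha 0.025, beta 0.20, 32 evaluable children, 40 enrolled, paired t test as basis. From Analyses: 0.025 for each co-primary outcome. Assumed: two-sided testing at 0.025, except where stated.

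**1. The plan's own figure.** n = ((z_alpha + z_power) × SD / difference)².
- One-sided 0.025: ((1.960 + 0.842) × 6/3)² = 31.4, so 32. This reproduces the stated number.
- Two-sided 0.025: ((2.241 + 0.842) × 6/3)² = 38.0, so 39. This does not.
- Drop-out: 32 / (1 − 0.20) = 40, as stated.

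Sidedness therefore matters for any power quoted below.

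**2. Post hoc power at the observed effect.** Set the noncentrality parameter of the t distribution to the observed t. With the critical value fixed, the result depends only on p and n.

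| p value | Observed difference, n = 32, SD 6 | Power, n = 32 | Power, n = 40 |
|---|---|---|---|
| 0.025 | 2.50 | 0.507 | 0.506 |
| 0.05 | 2.16 | 0.388 | 0.388 |
| 0.10 | 1.80 | 0.270 | 0.271 |
| 0.20 | 1.39 | 0.163 | 0.164 |
| 0.50 | 0.72 | 0.058 | 0.059 |

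In this version a result that misses significance shows power of about one half or less, and the sample size hardly matters.

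**3. Post hoc power at 3 points with the observed SD.** The noncentrality parameter is 3√n / SD.
- n = 32: 0.97 at SD 4, 0.68 at SD 6, 0.53 at SD 7.
- n = 40: 0.99, 0.79 and 0.65.

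This version varies with the data and is not fixed by p. But take two null results with n = 32 and observed SD 6, one with estimate 0.2 and one with 2.4. Both receive power 0.68.

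**4. The confidence interval for the same two results.** Half-width = t(0.9875, n − 1) × SD / √n.
- n = 32: 2.356 × 6 / √32 = 2.50 points.
- n = 40: 2.331 × 6 / √40 = 2.21 points.

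Estimate 0.2 gives 0.2 ± 2.5, that is −2.3 to 2.7, which excludes 3. Estimate 2.4 gives −0.1 to 4.9, which does not. At n = 32 a 3-point Lokomat benefit is excluded when the estimate is below 3 − 2.5 = 0.5. If the test is meant as one-sided 0.025, the matching interval is the 95% one, with half-widths 2.16 (n = 32) and 1.92 (n = 40).

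For the 6MWT, the Sample size section gives only a single-group gain of 25 m with SD 50 m. If that SD is assumed for the paired difference, the 97.5% half-width is 2.50 × 50/6 = 20.8 m (n = 32) or 18.4 m (n = 40).

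**5. How often the interval would settle the matter.** Suppose the true difference is zero and SD is 6. The 97.5% interval then lies wholly within ±3 points with probability 0.37 (n = 32) or 0.59 (n = 40), by simulation. The interval will often be inconclusive, but it will show that openly.

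**6. Baseline check.** No SD for the baseline A to baseline B shift is given. Assume 4 to 8 points and two-sided 0.05. The largest non-significant mean shift is t(0.975, n − 1) × SD / √n:
- n = 32: 2.040 × 4 / √32 = 1.44 up to 2.040 × 8 / √32 = 2.88 points.
- n = 40: 1.28 to 2.56 points.

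At the upper end, a shift close to the 3-point important difference could pass as equivalence.

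**The case against.** **The text does not say post hoc power will be used to interpret anything.** This stands. A reader might infer that a claim of no difference will rest on it, but the sentence only says the figure will be determined, and no equivalence claim is planned.

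**Circularity depends on a choice the text does not make.** This also stands. A reader might infer that every null result would be labelled underpowered. Step 3 shows otherwise if the 3-point target is used, since power can then reach 0.97 at n = 32. What survives is that neither version takes account of where the estimate lies relative to 3 points.

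**The baseline test has little weight.** Largely right. The article does not make it a condition for the primary analysis, and each period's own baseline enters the ANCOVA. A reader might suppose that the test pools the two sequences and so misses a shift that differs by first treatment. The text does not say it is pooled. The Analyses section also builds the order effect and its interaction with intervention into the main analysis and fits a GEE model with differential carryover. What remains is a test that cannot support the word equivalence, applied where no return to baseline is expected.

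**A condensed article may leave the reporting of intervals to the full plan.** True, and the absence of an interval rule is not the point. The point is the method that the article does commit to.

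**Conclusion.** The point holds as a criticism of a stated method, with consequences for interpretation only. Post hoc power is uninformative if computed at the observed effect (0.51, 0.27 and 0.06 at p = 0.025, 0.10 and 0.50). At 3 points it is informative about precision but silent on whether 3 points is excluded. The interval from the planned models answers that question, with a half-width of about 2.5 points at n = 32.

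These figures assume SD 6 for the paired difference, a simple paired analysis and two-sided alpha 0.025; covariate adjustment would change the half-width somewhat. It would be going too far to add that the trial's power is really 0.68 and a null result therefore likely. That figure needs two-sided 0.025, n = 32 and SD 6. Sidedness is not stated: one-sided 0.025 gives 0.78 at n = 32, and two-sided 0.025 with all 40 children gives 0.79.

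The superiority test and its type I error are unaffected. The baseline check is a minor companion point. The change should be made, but the trial's validity does not depend on it.

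**What to change.** 1. Delete the post hoc power sentence.
2. For null results, report the Lokomat-minus-PT difference with its 97.5% confidence interval from the planned models (or the level matching the test, once sidedness is stated). Read it against 3 points for the GMFM-66 and against a 6MWT difference fixed before the data are analysed. Claim no important difference only if the interval excludes that value; for a claim in both directions, the whole interval must lie within plus and minus it. Otherwise call the result inconclusive.
3. Report secondary outcomes by estimate and interval, without post hoc power.
4. Replace the baseline equivalence test by the mean baseline B minus baseline A shift, by sequence, with its confidence interval, and drop the word equivalence.

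No extra children, visits or models are needed. The intervals come from analyses already planned, and the only new decision is the 6MWT difference.

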A second analysis will include all who adhered to ≥50% of each intervention as well as those who discontinued one or both interventions for reasons noted in the primary efficacy analysis. The third analysis will be an “intent to treat”, including the last available data from all participants regardless of level of adherence or reason for withdrawal. As outlined above, a strong effort will be made to do a discharge assessment at time of withdrawal. Demographic characteristics, baseline scores and change scores of these three adherence groups will be evaluated to determine any systematic differences in their characteristics or outcomes.

Data from the session summary sheets will be compiled. Treatment categories, Lokomat parameter adjustments, and session activities will be summarized through graphic and tabular summaries, and related descriptive information from therapists’ comments will be reported.

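### The primary analysis set is defined in two conflicting ways, both selecting on attendance after randomisation, and the all-randomised analysis of this superiority trial ranks only third

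*Protocol article*

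**What the plan says.** The hypothesis is superiority: children should improve more with the Lokomat than with PT (protocol article, Study aims and hypothesis). The primary population is then defined twice.

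- **Sample size:** the primary efficacy analysis "focuses only on the children who attend more than 70% of the sessions within one or the other intervention phase". Children who discontinue are not mentioned.
- **Analyses:** "The primary analysis will include all children who attended ≥70% of sessions for each intervention". To these it adds children who gave up one or both interventions because of the study itself (fatigue and dislike are the examples) or left through an injury tied to an intervention. A child below 70% for any other reason is left out.

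The Analyses section then ranks two further sets. The second lowers the attendance limit to 50% of each intervention. The third, labelled intent to treat, is described as "including the last available data from all participants regardless of level of adherence or reason for withdrawal". The team will try hard to assess each child who withdraws.

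Families and treating therapists are not blinded (Blinding). The research assistant tells families the order (Randomisation) and follows attendance (Study interventions).

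**The concern.** A superiority claim should rest on the children as randomised. Here membership of the primary set depends on attendance and on a stated reason for leaving. Both arise after the family and therapist know which intervention is being given. If either is related to how a child responds to one intervention relative to the other, the retained children no longer give an unbiased comparison.

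Two further problems add to this. The document does not settle which children are in the set, so the choice could be made once attendance is known. The analysis that should serve as the check, the one on all participants, comes last and may fill missing periods with carried-forward values. In a cross-over trial, that would score an intervention the child never received as having produced no change.

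**Working it through.** **Inputs.** From the Design section: 16 sessions per intervention. From Sample size: target difference 3 points and SD 6.0 on the GMFM-66, alpha 0.025, beta 0.20, 32 evaluable children, 40 enrolled, and 20% for drop-out and protocol deviation together. Assumed: a gain of 5 points per block, with 3 points as an alternative. The only documented figure near 5 is for GMFM Stand and Walk in a single-group study (Sample size), not for the GMFM-66.

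**1. The plan's own figure.** n = (SD × (z_alpha + z_power) / difference)² = (6 × (1.960 + 0.842) / 3)² = 31.4, so 32. This reproduces with alpha 0.025 one-sided. With 0.025 two-sided, (6 × (2.241 + 0.842) / 3)² = 38.0, so 39. Then 32 / 0.80 = 40. The plan therefore allows for 8 of 40 children to be lost or excluded.

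**2. The two definitions side by side.** 70% of 16 is 11.2 sessions, so more than 70% and at least 70% both mean 12 sessions. That wording difference is harmless. The other two differences are not.

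| | Sample size | Analyses |
|---|---|---|
| Phases that must reach 12 sessions | one or the other | each |
| Study-related discontinuers and intervention injuries | not provided for (only attenders) | kept |

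A child with 14/16 (87.5%) Lokomat and 8/16 (50%) PT sessions, absent for non-study reasons, is in under the left column and out under the right.

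**3. How far the sets can differ.** Assume that a share p of children reaches 12 sessions in each phase, independently.

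- Each phase: 40p². For p = 0.80 and 0.90 this is 25.6 and 32.4, about 26 to 32 children on attendance alone.
- One or the other: 40 × (1 − (1 − p)²) = 38.4 and 39.6, about 38 to 40.

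Positive correlation between the two phases would narrow this gap, as would the discontinuers that the Analyses section keeps.

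**4. Selection in the primary set.** This was simulated with 20,000 trials of 40 children, no true difference, SD of the within-child difference 6, 8 children excluded, and a two-sided 0.025 test (1.25% per tail).

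- Exclusion at random: bias 0.0, false Lokomat win 1.2%.
- Exclusion correlated 0.5 with poor Lokomat change: bias +0.73 point, false Lokomat win 6.2%.
- Exclusion correlated 0.5 with poor PT change: bias −0.71 point, false PT win 6.1%.

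The correlation is an assumption. The simulation does not keep study-related discontinuers, so it probably overstates the effect for the Analyses definition.

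**5. The third analysis, if it carries values forward.** A child who never starts the second block gets change 0 instead of the gain g. With 20 children per sequence, bias (Lokomat minus PT) = g × (second-block PT losses − second-block Lokomat losses) / 40.

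| Second-block losses, PT / Lokomat | g = 5 | g = 3 |
|---|---|---|
| 8 / 0 | +1.0 | +0.6 |
| 6 / 2 | +0.5 | +0.3 |
| 4 / 4 | 0.0 | 0.0 |
| 2 / 6 | −0.5 | −0.3 |
| 0 / 8 | −1.0 | −0.6 |

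Under the same simulation settings with g = 5, false Lokomat wins are 10.0% at 8/0, 3.1% at 6/2 and 0.7% at 4/4. False PT wins are 10.5% at 0/8.

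**The case against.** The plan calls this an efficacy analysis, and the effect in children who attend is a fair question. It also limits the damage in several ways. The Analyses section keeps children who leave through dislike, fatigue or intervention injury, which are the losses most tied to treatment. Assessments on leaving are attempted. The co-principal investigators have no access to most outcome data during the trial. Three sets are analysed and their characteristics compared. A GEE analysis with treatment and period effects is also planned. Finally, each child is his or her own control, so exclusion biases the result only if it is related to the difference between the two responses.

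Most of this stands, and it makes the selection bias smaller. It does not remove it. Children who miss sessions for other stated reasons are still dropped, and the stated reason comes from people who know the treatment. An assessment on leaving cannot supply a second-block change for a child who never began that block. Comparing the sets describes their differences but does not restore the randomised comparison.

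Three stronger readings are tempting, and the documents do not support them.

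- **That the plan favours the Lokomat.** A reader might infer this because assured Lokomat access is a stated attraction (Design) and an earlier trial lost more than half of its control group (Background). That control group was PT only, whereas here every child is offered both interventions. Nothing shows in which sequence losses will fall.
- **That missing periods will be scored as zero.** The protocol speaks only of last available data. Carrying forward is the natural reading for a change score, but it is not stated.
- **That analysing all 40 children restores power from 0.68 to 0.79** (two-sided 0.025, SD 6). The 0.79 needs 40 complete pairs, and children who leave after the first block do not supply them. With 32 pairs and 8 Lokomat-first children seen only in the first block, a mixed model gives about 0.67 to 0.72 for within-child correlations from 0.8 down to 0.

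**Conclusion.** The point holds in this form. The two definitions of the primary set contradict each other and can classify the same child differently. Both select on attendance after randomisation, and the Analyses definition also on an unblinded reason for leaving. The all-randomised analysis is placed third.

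The possible bias has no established direction. For the third analysis it lies between −1.0 and +1.0 point, at most one third of the 3-point target, and is zero if losses are balanced. That range rests on three assumptions: that last available data means carrying forward, that each block gives 5 points, and that all 8 allowed losses occur before the second block starts. The 20% allowance also covers protocol deviations, so 8 such losses is an upper case within the plan. For the primary set, the simulated shifts of about 0.7 point either way depend on an assumed correlation and show only what selection of that strength could do.

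The contradiction needs no assumption and must be settled before the data are analysed.

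**What to change.** Make the primary analysis all randomised children as allocated. Use a mixed model on every observed period change score, including assessments made on leaving, with treatment, period, a random child effect, and the baseline covariate and order terms that the Analyses section already plans. Use no carried-forward values, and replace the last-available-data wording accordingly.

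Keep the 70% and 50% sets as sensitivity analyses. Use one definition, based on each intervention, in both Sample size and Analyses, with the same statement in both places about children who discontinue.

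The cost is rewording and reordering; no new data are needed. There are two drawbacks. The estimate includes poor attenders and may be slightly diluted. The model also relies on missing-at-random, which preference-driven drop-out would strain, so the report should state that reliance.
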